## Abstract

Background: Post-stroke epilepsy can reduce patients’ abilities to carry out various activities of daily living. Despite their importance in preventing the onset of post-stroke epilepsy, the prophylactic administration of antiepileptic drugs is controversial due to a lack of high-level clinical research. In this study, we initiated a prospective interventional study of prophylactic antiepileptic drug administration in patients with a subcortical hemorrhage, who are at the highest risk of developing epilepsy after experiencing a stroke. Methods: The study was conducted in a single-center setting and was a single-arm study with no control group; the case entry period started in November 2023 and is due to end in March 2025. Only cases with a subcortical hemorrhage will be included. The treatment regimen used in this study is 2 mg of perampanel per day. Perampanel will be administered for one year, followed by two years of follow-up, for a total study period of three years. The primary endpoint will be the development of epilepsy. Results: Perampanel administration is expected to reduce the incidence of post-stroke epilepsy in comparison to the results of previous reports on the use of alternative treatments. Conclusions: The results of this study will provide new insights into the prevention of post-stroke epilepsy. The relatively small size of this study makes it difficult to provide strong evidence of the efficacy of perampanel, but it may serve as a basis for larger clinical trials.

## 1. Introduction

A stroke may consist of cerebral infarction, a cerebral hemorrhage, or a subarachnoid hemorrhage; patients may subsequently develop new-onset epilepsy, which is also referred to as post-stroke epilepsy. This is reported to occur in 5–10% of stroke survivors. The number of new post-stroke epilepsy cases in Japan is estimated to be approximately 10,000 per year, so it is by no means a rare disease [1].

Post-stroke epilepsy can cause a decrease in the ability of patients who have survived the acute stage of a stroke—that is, stroke survivors—to carry out various activities of daily living (ADLs), and so preventing and treating post-stroke epilepsy are particularly important. There have been many reports on the risk factors associated with developing post-stroke epilepsy [2,3,4], but there are only a few reports on potential drug therapies that can prevent post-stroke epilepsy [5,6]. The Japanese guidelines mention the prophylactic administration of antiepileptic drugs for high-risk cases [7], but they only state that “administration may be considered,” and both the number of recommendations for this treatment modality and evidence of its efficacy are limited.

Furthermore, there are no drugs approved for prophylactic use, and doses and administration periods have also yet to be optimized. Although the American Stroke Association (ASA) guidelines mention the prophylactic administration of antiepileptic drugs for the treatment of a subarachnoid hemorrhage [8], there are few recommendations for this use and there is no mention of specific drugs or administration periods. According to the ASA, the prophylactic administration of drugs is currently being carried out across the world, but this prevalence is unknown.

The aim of this study is to demonstrate the effectiveness of the prophylactic administration of antiepilepsy drugs for the treatment of post-stroke epilepsy. In this study, the drug under investigation is perampanel. This drug was chosen due to the fact that it is regarded as the most analogous pharmaceutical agent to the pharmacological mechanism of post-stroke epilepsy. The specifics of the selected drug are outlined in Section 3.2.

The results of this study will provide new insights into the prevention of post-stroke epilepsy and will significantly contribute to preventing a decline in the ability of stroke survivors to perform ADLs. This study’s organization is shown in jRCTs051230107 on 4 October 2023.

## 2. Experimental Design

### 2.1. Study Design and Setting

The aim of this study is to evaluate the usage of perampanel for the prevention of post-stroke epilepsy in patients with a subcortical hemorrhage in a single-center, single-arm study. The rationale for conducting a single-arm study without a placebo group is that we anticipate it to be challenging to recruit the requisite number of patients at the study sites. Further details are provided in Section 2.4. All participants will be recruited from the Department of Neurosurgery at Nara Medical University Hospital (Kashihara, Japan).

### 2.2. Eligibility Criteria

The target stroke type is limited to subcortical hemorrhages. We believe that this will allow us to observe the effectiveness of prophylactic administration. Within the existing literature, including in a previous study by our group, it has been reported that a subcortical hemorrhage is the most common cause of post-stroke epilepsy [2,3,4,9]. A diagnosis of a subcortical hemorrhage is made through the use of computed tomography (CT) or magnetic resonance (MR) imaging of the head during the patient’s initial admission to hospital. A cerebral subcortical hemorrhage is defined as a hemorrhage involving the cortex of the frontal, temporal, parietal, and occipital lobes. The CAVE score is a well-established risk assessment measure that is used to predict the onset of post-stroke epilepsy in patients with a cerebral hemorrhage [10]. However, the CAVE score includes the occurrence of early seizures, and patients who experience an early seizure should receive antiepileptic drugs immediately, rendering these patients unsuitable for inclusion in this study. Consequently, the CAVE score will not be utilized in the selection of patients for this study.

Patients with a subcortical hemorrhage who are available for registration in the study within 1 week, whose age at the onset is between 50 and 90 years, who are capable of taking drugs orally, including via tube feeding, who have been fully informed of the details of this clinical research, and who have given their written consent, either themselves or through a surrogate, are eligible for inclusion in this study.

Exclusion criteria include subjects with a history of epilepsy; patients currently taking antiepileptic drugs; patients whose cerebral hemorrhage is known to be caused by a vascular malformation such as arteriovenous malformation or Moyamoya disease (CT angiography, MR angiography, or digital subtraction angiography can be utilized for the diagnosis of vascular malformations) or is traumatic in nature; patients with a severe renal or hepatic impairment; patients who are pregnant or breast feeding; patients with an allergy to the target drug; and those judged to be inappropriate as research subjects by the principal investigator.

### 2.3. Discontinuation of Interventions

The investigator will discontinue the study if any of the following criteria are met: the onset of epilepsy, worsening complications, the development of a disease which is suspected of being as a result of this research, pregnancy, an allergy to the test drug, severe renal or hepatic dysfunction, difficulty in continuing to take the drug, and/or the research subject is deemed ineligible to continue oral administration for other reasons. The investigator will withdraw patients from the study if any of the following conditions are met: a research subject requests to be removed from the study or withdraws consent, a research subject is not eligible after registration, the entire study is canceled, and/or the doctor deems it appropriate to cancel the study for other reasons.

### 2.4. Sample Size

About 40 patients with a subcortical hemorrhage are admitted to the Nara Medical University hospital per year. During each registration period, which lasts for one year and six months, 54 patients (90% of 60 patients) are expected to be registered. Taking a drop-out ratio of 10% into account, approximately 48 patients will be eligible for analysis during the 3-year observation period.

Based on previous research, we know that the rate of developing epilepsy within three years after a stroke is approximately 20% [9,10,11]. If the incidence of post-stroke epilepsy can be suppressed to less than 10%, or to a maximum of 4 out of 48 cases, by the prophylactic administration of perampanel, the upper limit of the 95% confidence interval will be less than 20%, suggesting a certain level of effectiveness.

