### 2.6. Statistical Methods

The number and proportion of epilepsy cases three years after the initiation of treatment will be counted, and the 95% confidence interval of the incidence rate will be calculated using the Clopper–Pearson method. The subjects used to calculate these proportions are those in the analyzed population who have survived for up to three years following the initiation of treatment who are available for follow-up, or those who have developed epilepsy within three years of initiating treatment.

In addition, as a secondary analysis, a Kaplan–Meier curve will be drawn for the number of days until the onset of epilepsy starting from the beginning of the treatment protocol, and the incidence rate of epilepsy within the three-year study period and its 95% confidence interval will be calculated using Greenwood’s calculation formula. At that time, patients who are unable to be followed-up with or who have died will be excluded from the analysis. We will also perform a secondary analysis with mortality as a competing risk.

Regarding the above two analyses, we will also conduct separate analyses for the Glasgow Coma Scale (GCS) and the National Institutes of Health Stroke Scale (NIHSS).

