## 4. Expected Results

The expected results of our study include a significantly lower incidence of post-stroke epilepsy in patients treated with perampanel than previously reported (5 to 10%). It may be feasible to ascertain certain risk factors for the emergence of post-stroke epilepsy based on data gathered at the time of admission. In particular, patients with high scores on the GCS and NIHSS are more likely to have extensive brain lesions and may be more susceptible to developing post-stroke epilepsy.

If the number of patients included in the study is small, there may be no cases of post-stroke epilepsy. In this case, it may be difficult to perform statistical analyses. However, these results may facilitate the design and planning of larger prospective studies, and this study may serve as a basis for subsequent studies that can provide more solid evidence. Although the existence of post-stroke epilepsy has been known for some time, there is very little evidence to support the prophylactic use of antiepileptic drugs to treat this condition. This may be due to the difficulty of conducting high-level prospective clinical trials. The complexity of the different pathological states of stroke patients, the complexity of the prognosis of individual patients, and the fact that, unlike other diseases, these patients are often transferred to other hospitals or rehabilitation centers instead of being discharged because of their reduced ability to perform ADLs as a result of the stroke, which makes follow-up difficult, may contribute to the difficulty in conducting this type of research. The results of this relatively small study are expected to be very significant. We hope that the success of this study will serve as a basis for new research in the future, and it is our hope that the aggregation of these studies will yield compelling evidence.

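### The limit of 4 events in 48 patients has no slack, the stated entry dates give about 46 analysable patients, and a rate below 10% does not guarantee an upper limit below 20%

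*Protocol article*

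**What the plan says.** Section 2.4 builds the sample size from four inputs:

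- Admissions: "About 40 patients with a subcortical hemorrhage are admitted to the Nara Medical University hospital per year".
- Period: "During each registration period, which lasts for one year and six months".
- Registration: "54 patients (90% of 60 patients) are expected to be registered".
- Loss: "Taking a drop-out ratio of 10% into account, approximately 48 patients will be eligible for analysis during the 3-year observation period".

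It then takes a historical three-year epilepsy rate of about 20%. Its condition for effectiveness has two forms. One is an incidence below 10%; the other reads as follows: "or to a maximum of 4 out of 48 cases, by the prophylactic administration of perampanel, the upper limit of the 95% confidence interval". Under either form that limit is said to lie below 20%, which the plan would regard as some evidence of effectiveness.

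The Abstract dates enrolment differently: "the case entry period started in November 2023 and is due to end in March 2025".

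Section 2.6 fixes the Clopper–Pearson method for the primary 95% interval. It restricts the denominator to patients "who have survived for up to three years following the initiation of treatment who are available for follow-up", plus those who developed epilepsy within three years.

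**The concern.** The trial has one arm and no control, so comparing the upper confidence limit with 20% is its only benchmark for effectiveness. Section 2.4 turns that benchmark into an expected number of patients and a maximum number of events. Three things make these figures unreliable as written:

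- The event limit works only at 48 or more analysable patients, and 48 is itself an approximate figure built on a rounded admission rate.
- The registration period in Section 2.4 is longer than the entry period in the Abstract.
- The 10% incidence is offered as if it secured the upper limit by itself, which is true only for some sample sizes.

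At stake is whether readers and the investigators carry forward an event limit and a chance of success that the design, on its own figures, does not deliver.

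**Working it through.** **Inputs.** Section 2.4: 40 admissions a year, 18 months, 90% registered, 10% drop-out, comparison rate 20%, at most 4 events in 48. Abstract: November 2023 to March 2025. Section 2.6: Clopper–Pearson, 95%, taken as two-sided.

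**Step 1: reproduce the plan's number.** 40 × 1.5 = 60 admitted; 60 × 0.9 = 54 registered; 54 × 0.9 = 48.6, stated as about 48. It reproduces.

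**Step 2: reproduce the plan's limit.** The upper limit for x events in n patients is the 0.975 quantile of a Beta(x + 1, n − x) distribution. For 4/48 it is 19.98%. The statement is correct at 48, by 0.02 percentage points.

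**Step 3: vary the number of patients.**

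| Events / n | Observed rate | Upper limit | Below 20%? |
|---|---|---|---|
| 4/48 | 8.3% | 19.98% | yes |
| 4/47 | 8.5% | 20.38% | no |
| 4/46 | 8.7% | 20.79% | no |
| 4/41 | 9.8% | 23.13% | no |
| 3/46 | 6.5% | 17.90% | yes |
| 3/41 | 7.3% | 19.92% | yes |
| 3/40 | 7.5% | 20.39% | no |
| 2/34 | 5.9% | 19.68% | yes |
| 2/33 | 6.1% | 20.23% | no |
| 5/51 | 9.8% | 21.41% | no |
| 5/54 | 9.3% | 20.30% | no |
| 5/55 | 9.1% | 19.95% | yes |

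So the maximum is 2 events for 34–40 patients, 3 for 41–47 and 4 for 48–54.

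**Step 4: apply the Abstract's dates.** From 1 November 2023 to 31 March 2025, the longest reading, is 17 months. 40 × 17/12 = 56.7 admitted; × 0.9 = 51.0 registered; × 0.9 = 45.9, about 46 analysable. At 46 the maximum is 3 events.

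**Step 5: chance of meeting the criterion (exact binomial).**

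| True rate | n = 48, at most 4 events | n = 46, at most 3 events |
|---|---|---|
| 8.33% (4/48) | 62.9% | 45.9% |
| 10% | 46.9% | 31.2% |

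The drop arises because the permitted count steps from 4 to 3. The chance does not move steadily with n: at 54 patients, with 4 events still the limit, it is 52.8% for a true rate of 8.33%.

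**Step 6: the 10% condition.** At 48 it agrees with the event limit, since 4/48 = 8.3% and 5/48 = 10.4%. It also suffices at 49 and 50. Elsewhere it can fail: 4 events at every n from 41 to 47, and 5 events at every n from 51 to 54, are below 10% with an upper limit above 20%.

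**Step 7: the denominator rule.** Section 2.6 leaves out event-free patients who die or are lost. If the 10% drop-out already covers them, nothing further is lost. If it does not cover deaths, the loss depends on mortality, which the documents do not give. As an assumption only, event-free mortality of 5%, 10% or 20% on top of the 10% would leave 43.6, 41.3 or 36.7 patients over 17 months (46.2, 43.7 or 38.9 over 18). The maximum would then be 3, 3 or 2 events in either case.

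**The case against.** The best defence is that Section 2.4 contains no arithmetic error: the accrual gives 48.6, the limit for 4/48 is below 20%, and at 48 the two forms of the condition coincide. That stands. The inputs are also openly rounded. About 42 admissions a year (48 ÷ (17/12 × 0.81) = 41.8) would restore 48 in 17 months. That stands too, and it limits the size of the point. It does not remove it, because a limit that fails with one patient fewer cannot rest on an approximate number.

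Three stronger readings are tempting and are not supported.

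- A reader might infer that four events would be declared a success while the interval crosses 20%. Section 2.4 ties four events to 48 cases, and Section 2.6 computes the interval on the actual denominator, so 4/46 would be reported with its limit of 20.8%. False success is not automatic.
- A reader might infer that the denominator rule certainly brings the number below 48, given patients aged 50–90, the 80% adherence requirement in Section 3.2, and the follow-up difficulty conceded in Section 4, where "these patients are often transferred to other hospitals or rehabilitation centers instead of being discharged". But the 10% leads to patients eligible for analysis and may cover all of these. Section 3.2 also does not say that adherence exits leave the analysis. Only the direction is certain.
- A reader might infer that every rate below 10% fails at 41–47 patients. It does not: 3 events pass throughout that range.

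A less conservative interval would give some room (Wilson passes 4 events at 47), but the protocol fixes Clopper–Pearson, and at 46 Wilson also fails (20.32%).

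**Conclusion.** The point holds at moderate severity. On the document's own figures, the Abstract's dates deliver about 46 analysable patients rather than 48, and the permitted number of events is then 3, not 4. At a true rate of 8.3% the chance of meeting the criterion is 46% rather than 63%. Separately, the 10% condition is wrong as a general sufficient condition, whichever period is right.

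The conclusion rests on 40 admissions a year, 90% registration, 10% drop-out, a two-sided 95% Clopper–Pearson interval, and 17 months as the longest reading of the dates. The shortfall shown is about two patients. Any further loss through deaths or other exits is an assumption, because the documents do not say what the 10% covers. The planned primary estimate and interval are unaffected, and the article itself presents the study as too small for strong evidence.

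**What to change.** In Section 2.4:

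1. Reconcile the 18-month registration period with the Abstract's dates, and restate the expected analysable number: about 46 if 17 months stands.
2. Say whether the 10% drop-out covers event-free deaths, losses and adherence exits. If it does not, give the further loss assumed.
3. Delete the incidence below 10% as a sufficient condition.
4. State the criterion as a Clopper–Pearson upper 95% limit below 20% at the achieved denominator: at most 2 events for 34–40 patients, 3 for 41–47, and 4 for 48–54.

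This costs protocol wording only and needs no extra patients. If 17 months is confirmed, the stated threshold becomes less favourable. The change is best made before outcomes are known.

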### 2.5. Data Collection and Management

The results will be collected by the investigators or outcome assessors using a case report form (CRF). The investigator will evaluate patients’ eligibility using routine blood and image examinations. An investigator will ask the participants or proxies about their medication status, the occurrence of epileptic seizures or a stroke, their survival status, and the occurrence of other adverse events every three months by telephone after the initiation of the treatment protocol. Epileptic seizures are defined as the acute onset of tonic or clonic motor convulsions, absence seizures leading to an attenuation of consciousness or a loss of consciousness, automatism, sensory abnormalities, and autonomic neurological symptoms. The investigator will determine whether the symptoms are indicative of epileptic seizures based on the information provided by the patient or a witness. The diagnosis of post-stroke epilepsy is based on the occurrence of a single seizure. Typically, epilepsy is diagnosed based on the occurrence of two or more seizures that occur at a certain interval. However, as reported by Fisher et al., post-stroke epilepsy can be diagnosed based on a single seizure due to its high recurrence rate [12]. This study also adopted this diagnostic criterion.

All information in the study protocol will be collected by the investigator during the study period and recorded on CRFs that will be stored at the Nara Medical University data center.

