### 3.3. Participant Timeline

All outcomes will be evaluated, and data will be collected according to the participant’s timeline (Table 1). Neurological findings, blood tests, and imaging studies will be performed when a patient enters the study to confirm whether or not the patient is eligible to participate in the study. After the completion of the drug administration protocol, the patients will be followed-up with for another 2 years. Patient status should be checked every 90 days (allowed within ± 10 days) during the administration and follow-up periods and it will be confirmed through a telephone interview or outpatient visit. During the follow-up, patients will be checked for survival, the occurrence of seizures, the occurrence of another stroke, and adverse events.

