### 3.4. Outcomes

The primary endpoint will be the percentage of patients who develop epilepsy within the first three years after the initiation of the treatment protocol. According to the International League Against Epilepsy, the definition of epilepsy, with a high likelihood of a persistently lowered seizure threshold and therefore a high risk of recurrence of events such as a stroke, is the occurrence of at least one epileptic seizure [10]. The secondary endpoints will be all-cause mortality within three years after the initiation of the treatment protocol and the occurrence of another stroke (cerebral infarction, cerebral hemorrhage, subarachnoid hemorrhage) within three years of starting the treatment protocol (regardless of whether this is a new stroke or a recurrence).

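### Each 90-day seizure check may rest on the participant or a proxy alone, although one seizure with impaired awareness counts as a primary-endpoint case; missed cases make the below-20% criterion easier to meet

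*Protocol article*

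**What the plan says.** Section 3.4 of the protocol article defines the endpoint: "The primary endpoint will be the percentage of patients who develop epilepsy within the first three years after the initiation of the treatment protocol". Section 2.5 sets the threshold for a case: "The diagnosis of post-stroke epilepsy is based on the occurrence of a single seizure". Besides tonic or clonic convulsions, the qualifying seizures include "absence seizures leading to an attenuation of consciousness or a loss of consciousness, automatism, sensory abnormalities, and autonomic neurological symptoms".

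Section 2.5 also fixes how these events are found. "An investigator will ask the participants or proxies about their medication status, the occurrence of epileptic seizures or a stroke", and this happens "every three months by telephone after the initiation of the treatment protocol". The investigator then decides whether an event was a seizure "based on the information provided by the patient or a witness". Section 3.3 describes the same 90-day check slightly differently: "it will be confirmed through a telephone interview or outpatient visit". Table 1 lists 12 such contacts.

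Section 2.2 admits patients aged 50 to 90, including those fed by tube and those whose consent comes from a surrogate. Section 2.4 takes about 20% as the historical three-year rate and treats at most 4 cases in 48 as suggesting effectiveness, because the upper 95% limit is then below 20%.

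**The concern.** The event definition and the way events are found do not fit together well. A person who loses awareness in a seizure may not know that it happened. An observer, in turn, cannot see a purely sensory event. Because the informants are joined by an 'or', a call to one of them completes the check, and a patient can be recorded as seizure-free on the word of someone who could not have known about part of what the endpoint counts.

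In a randomised comparison, incomplete detection would affect both arms. Here the comparator is a fixed external rate, so no concurrent group shares the loss. Each undetected case moves the observed proportion down and the upper confidence limit with it, which is the direction of declared success. The criterion has almost no slack, so a small loss can matter.

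**Working it through.** **Inputs.** From Section 2.4: 40 admissions a year, 18 months of registration, 90% registered, 10% drop-out, benchmark 20%, success at 4 or fewer of 48. From Section 2.6: two-sided 95% Clopper–Pearson interval. Not in the document, and therefore assumed: the detection share s, the proportion of true cases identified at least once during the three years.

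**1. The plan's own figures.** 40 × 1.5 = 60; 60 × 0.9 = 54; 54 × 0.9 = 48.6, or about 48 as stated. The Clopper–Pearson upper limit for x cases in n is the 97.5% quantile of Beta(x + 1, n − x).

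| Observed cases of 48 | Proportion | Upper 95% limit | Below 20%? |
|---|---|---|---|
| 2 | 4.2% | 14.25% | yes |
| 3 | 6.3% | 17.20% | yes |
| 4 | 8.3% | 19.98% | yes |
| 5 | 10.4% | 22.66% | no |
| 6 | 12.5% | 25.25% | no |

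The stated rule reproduces. The boundary lies between 4 and 5 cases, and 4 passes by 0.02 percentage points.

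**2. Effect by count.** With the denominator held at 48, five true cases fail and one missed case turns that into a pass. With six true cases, two must be missed. Read from the observed side, the number of undetected cases that would lift the limit above 20% is 5 − x: one if 4 are observed, two if 3, three if 2.

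**3. Effect by probability.** If the true incidence is p and a share s of cases is detected, the observed count is Binomial(48, p × s). The chance of meeting the rule is P(X ≤ 4).

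| Detection share s (assumed) | p = 20%: observed rate | p = 20%: P(X ≤ 4) | p = 15%: P(X ≤ 4) |
|---|---|---|---|
| 100% | 20% | 2.5% | 13.4% |
| 90% | 18% | 5.1% | 20.6% |
| 80% | 16% | 9.9% | 30.2% |
| 70% | 14% | 17.9% | 42.3% |
| 60% | 12% | 30.2% | 56.4% |

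At p = 20% the drug has no effect relative to the benchmark, so that column is the false-success rate. It roughly doubles at 90% detection (5.1 / 2.5 ≈ 2).

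**4. What the shares mean.** They apply to cases, not to single seizures. A patient with several seizures needs only one of them reported, so the share of cases found is at least as high as the share that a single event would suggest.

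**The case against.** The 'or' can be read benignly: whoever is able to inform will be asked. Proxies, witnesses, surrogates and outpatient visits are all provided for, and a condensed article may leave call scripts and form fields to the full protocol. That stands to this extent: a patient-only contact is allowed, not prescribed. A reader might infer that incapable patients will be asked alone; the article does not say so. But the rule it does state accepts a single informant.

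The size of any bias is not established. The detection shares are assumed, and the document does not say how cases were found in the studies behind the 20%. If those were equally incomplete, the bias shrinks. One missed case changes the outcome only when there are exactly five true cases, and every threshold rule has such a boundary.

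The net direction is not established either. A single reported sensory or autonomic symptom can count, so non-epileptic symptoms could be scored as cases and work against the drug.

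Two further inferences are tempting. One is that detection differs by neurological severity and so distorts the separate GCS and NIHSS analyses in Section 2.6. That is plausible, but nothing in the document shows it. The other draws on the remark in Section 4 that "these patients are often transferred to other hospitals or rehabilitation centers instead of being discharged". This is a general comment on why such research is difficult, and a facility with staff may observe patients more closely, not less.

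**Conclusion.** The point holds as an inexpensive improvement to a stated data-collection rule. The endpoint counts events that one informant may be unable to report, the plan accepts one informant, and missed cases act toward success in a single-arm trial whose limit at 4 of 48 is 19.98%. The illustrative rise in the false-success rate, from 2.5% to 5.1% at 90% detection and 9.9% at 80%, assumes a true incidence of 20%, 48 analysed patients, no over-reporting, and a benchmark that was fully ascertained.

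A reader might conclude that the trial is shown to be biased in favour of perampanel. The document does not support that: it gives no detection rate and no ascertainment method for the benchmark, and errors in the other direction are possible. What is shown is a vulnerability that the present rule leaves open and that later analysis cannot repair, because seizures never reported cannot be recovered.

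**What to change.** **Collection.** In Section 2.5, and in the same words for both contact modes in Section 3.3, have the investigator ask the participant where able and, where one exists, a proxy, caregiver or facility staff member who observes the participant. State that a contact without an observer still counts as completed follow-up and is flagged, so that it does not become missing and remove the patient from the analysis set in Section 2.6. Make the two sections agree on whether outpatient visits are a contact mode.

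**Recording.** Add two fields to the case report form for each contact: who informed, and the seizure type if one is reported (motor, impaired awareness, sensory or autonomic).

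**Reporting.** Give the share of contacts that had an observing informant. Beside the primary proportion, show a sensitivity range for missed cases, for example the number of undetected cases that would lift the upper limit above 20%.

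**What not to add.** A motor-seizures-only analysis should not be tested against 20%. It can only keep or lower the count while the benchmark is not restricted in that way, so it leans toward success. A subset of patients whose contacts all had an observer is selected after baseline and should be descriptive only.

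**Cost.** A longer call, or a second one, at each of up to 12 contacts per patient, plus an amendment that needs committee review under Section 3.5.3. Enrolment began in November 2023, so only contacts after the amendment benefit. No new visits or procedures are needed.
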